#### **STAGE 3**

**Primary Outcome measures.** Co-primary outcome measures include survival, defined as time to death, tracheostomy or the initiation of permanent assisted ventilation (PAV) and change in function as measured by ALSFRS-R. Non-invasive ventilation techniques utilized for more than 22 hours daily for more than one week will be the criterion for determining PAV. The primary analysis will be by "intention to treat." We will ascertain the status of all subjects at the end of the study and every subject will be included in the analysis whether or not they elected to stop treatment before the end of the study. The analysis of survival will use a log-rank test stratified by riluzole use. The use of the log-rank test and a design where everyone is treated until the end of the study has several advantages over treating everyone for only 52 weeks and using the 52-week mortality. By enrolling subjects at a constant rate in over an approximate 24-month enrollment period, we will be able to follow subjects anywhere from 12-36 months, with an average of 18 months of on-treatment follow-up. This is close to estimated median survival time found in previous ALS studies [95]. The power of tests comparing survival distributions depends on the number of events during the trial. Thus there are substantial power advantages

for treating people for a longer duration. To examine the co-primary endpoints jointly, our primary analysis strategy is to use the “shared parameter” model described in Vonesh, Greene and Schluchter[148]. This is described in more detail below in Section 9.1.3. The data analysis will be based on the ALSFRS-R during the first 12 months of treatment.

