### *Analysis of Secondary Outcome Variables*

**Safety and Tolerability.** The safety data will be summarized by treatment group. The treatment groups will be compared with respect to occurrence of each adverse event. Total number of adverse events and abnormal laboratory tests will be compared between groups using Fisher's exact test. Withdrawal, abnormal laboratory tests, vital signs and use of concomitant medications will be assessed to characterize the safety profile of ceftriaxone. Compliance data will be determined for each visit and by treatment group. The time to subject refusal will be compared between treatment groups in order to better determine tolerability. This will be accomplished using a method of survival analysis that allows informative censoring due to death [188]. Descriptive statistics denoting the changes from baseline to the final assessment visit with respect to key laboratory parameters and vital signs will also be provided.

**VC, Dynamometry and Quality of Life.** Our primary analysis strategy is to use a random effects analysis of variance using PROC MIXED in SAS [189]. The basic idea of this model is that each subject has his or her own trajectory with a random, slope, intercept and curvature the average value of which may depend on treatment. Since the subject groups start out the same, the intercept will not depend on treatment but the slope and curvature may. In our trial of topiramate this model was sensitive to a negative effect on muscle strength on treatment.

There was a significant curvature but only the slope was affected by treatment. The advantage of using this model is that it accommodates the variable duration of follow-up that will result from our trial design. We will look carefully at the residuals for this model to be sure that it fits the data. If there appear to be problems with fit, we will use a robust approach of assessing significance where the p-value for any treatment contrast is calculated using a permutation test.

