## 10.4 Adverse Experiences Monitoring and Reporting

An adverse event (AE) is any unfavorable and unintended sign (including a clinically significant abnormal laboratory finding, for example), symptom, or disease temporally associated with a study, use of a drug product or device whether or not considered related to the drug product or device.

The adverse event (AE) definitions and reporting procedures provided in this protocol comply with current CFR 21 Part 312 and device regulations CFR 21 Part 812. The Site Investigator will carefully monitor each subject throughout the study for possible adverse events. All AEs will be documented on eCRFs designed specifically for this purpose. It is also important to report all AEs, especially those that result in permanent discontinuation of the investigational drug being studied, whether serious or non-serious.

For the purposes of this study, symptoms of progression/worsening of ALS, including 'normal' progression, will be recorded as adverse events. The following measures of disease progression will not be recorded as adverse events, even if they worsen (they are being recorded and analyzed separately): vital capacity results, HHD results, grip strength results, and ALSFRS-R ratings.

Subjects will be monitored for adverse events from the time they sign consent until completion of their participation in the study. Relationship of adverse experiences to the experimental intervention will be assessed at each in-person and telephone study visit by recording all voluntary complaints of subjects and by assessment of the clinical features of ALS. Attention will be directed to clinical adverse experiences associated with prior ceftriaxone studies, as well as any evidence of unexpected worsening of the underlying ALS. Laboratory surveillance tests will be obtained as outlined above.

A serious adverse event is defined as an adverse event that meets any of the following criteria:

- Results in death
- Is life threatening: that is, poses an immediate risk of death as the event occurred  
This serious criterion applies if the study subject, in the view of the Site Investigator, is at substantial risk of dying from the AE as it occurs. It does not apply if an AE hypothetically might have caused death if it were more severe.
- Requires inpatient hospitalization or prolongation of existing hospitalization.  

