#### ***10.4.1 Evaluating and Recording of Adverse Events***

---

At each visit all adverse events that are observed, elicited by the Site Investigator, or reported by the subject will be recorded in the appropriate section of the Adverse Event log, entered into the EDC and evaluated by the Site Investigator.

Minimum information required for each AE includes type of event, duration (start and end dates), severity, seriousness, causality to study drug, action taken, and outcome.

The Site Investigator will grade the severity of AEs. The severity grading will be based on the unique clinical descriptions of severity for each AE in the CTCAE system, which follows this general guideline:

|         |                                  |
|---------|----------------------------------|
| Grade 1 | Mild AE                          |
| Grade 2 | Moderate AE                      |
| Grade 3 | Severe AE                        |
| Grade 4 | Life-threatening or disabling AE |
| Grade 5 | Death related to AE              |

---

The relationship of the AE to the study drug should be specified by the Site Investigator, using the following definitions:

1. Not Related: Concomitant illness, accident or event with no reasonable association with treatment.
2. Unlikely: The reaction has little or no temporal sequence from administration of the study drug, and/or a more likely alternative etiology exists.
3. Possibly Related: The reaction follows a reasonably temporal sequence from administration of the drug and follows a known response pattern to the suspected drug; the reaction could have been produced by the study drug or could have been produced by the volunteer's clinical state or by other modes of therapy administered to the volunteer.
4. Probably Related: The reaction follows a reasonable temporal sequence from administration of study drug; is confirmed by discontinuation of the study drug or by rechallenge; and cannot be reasonably explained by the known characteristics of the volunteer's clinical state.
5. Definitely Related: The reaction follows a reasonable temporal sequence from administration of study medication; that follows a known or expected response pattern to the study medication; and that is confirmed by improvement on stopping or reducing the dosage of the study medication, and reappearance of the reaction on repeated exposure.

---

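### Fisher's exact test is assigned to totals of adverse events and abnormal laboratory tests without saying whether subjects or events are counted, and with no allowance for follow-up time

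*Combined protocol and SAP*

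**What the plan says.** Under Analysis of Secondary Outcome Variables in section 9.1.3, the safety paragraph has two consecutive sentences on adverse events. The first names no test: "The treatment groups will be compared with respect to occurrence of each adverse event". The second does: "Total number of adverse events and abnormal laboratory tests will be compared between groups using" Fisher's exact test. Neither says whether the two-by-two table counts subjects or events, or what the denominator is.

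Three other places bear on this:

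- Section 10.4.1 collects recurrent events: "At each visit all adverse events that are observed, elicited by the Site Investigator, or reported by the subject will be recorded". Section 10.4 adds that "symptoms of progression/worsening of ALS" are recorded as adverse events.
- Section 10.4 sets the observation period: "Subjects will be monitored for adverse events from the time they sign consent until completion of their participation in the study".
- Section 6.3.4, STAGE 3, gives the length of that period: "we will be able to follow subjects anywhere from 12-36 months, with an average of 18 months of on-treatment follow-up".

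The same part of section 9.1.3 does deal with censoring by death for time to subject refusal, and with unequal follow-up for vital capacity, dynamometry and quality of life. It makes no such provision for adverse events.

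**The concern.** Occurrence has already been covered by the first sentence, so the literal sense of a total number in the second is a count. A count that can exceed the number of subjects has no valid two-by-two table. If events are nevertheless entered as independent units, the p-value ignores the fact that some subjects contribute many more events than others.

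Clustering is built into the design. By the Schedule of Assessments, safety laboratory tests are drawn at weeks 1, 2 and 4 and then every four weeks. That is 15 post-baseline draws by week 52 (2 + 13) and 41 by week 156 (2 + 39). A persistently abnormal value in one subject would be counted again and again.

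A separate issue is exposure. A subject who lives longer is observed longer and has more chance to report an event. Long-term safety is a named secondary outcome, and what is at stake is whether a reported difference in adverse events reflects the drug.

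**Working it through.** The documents attach no error rate, power or event rate to this comparison, so there is no stated figure to reproduce. The two readings were compared by simulation.

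**Inputs from the documents**

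- Allocation: 540 subjects at 2:1 give 360 and 180. The 60 STAGE 1 subjects at 1:1:1 give 40 and 20. The total is 400 active and 200 placebo.
- Planned follow-up: 12 to 36 months, taken as uniform.
- One-year survival of 75% (section 9.1.3), so the hazard is −ln 0.75 = 0.288 per year.
- Design effect: a 50% longer median, so the hazard on drug is 0.288/1.5 = 0.192 per year.

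**Assumed, not in the documents**

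- Two-sided 0.05.
- Adverse event rate m of 0.15 to 6 per subject-year, identical in both arms.
- Gamma-distributed between-subject variation with variance d of 0 to 1.
- Adverse event observation ends at the survival event.
- The longer follow-up of STAGE 1 subjects is ignored.

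**Follow-up time.** Mean follow-up is the average of (1 − exp(−λC))/λ over C from 1 to 3 years, that is [1 − (exp(−λ) − exp(−3λ))/(2λ)]/λ.

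- Placebo: [1 − (0.750 − 0.422)/0.575]/0.288 = 1.49 years (17.9 months).
- Drug under the design effect: [1 − (0.825 − 0.563)/0.384]/0.192 = 1.64 years (19.7 months).
- Ratio: 19.7/17.9 = 1.10.

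**Equal survival, no true difference: proportion of trials rejected (1000 replicates)**

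| m per year | d | Events vs person-time | Events vs 2:1 split | Events over visits | Subjects with ≥1 event |
|---|---|---|---|---|---|
| 0.15 | 0 | 0.041 | 0.053 | 0.043 | 0.048 |
| 0.15 | 1 | 0.079 | 0.092 | 0.080 | 0.047 |
| 0.5 | 1 | 0.160 | 0.180 | 0.165 | 0.044 |
| 3 | 0.5 | 0.325 | 0.399 | 0.398 | 0.040 |
| 3 | 1 | 0.422 | 0.454 | 0.478 | 0.044 |
| 6 | 0 | 0.047 | 0.289 | 0.135 | 0.041 |
| 6 | 0.5 | 0.450 | 0.512 | 0.569 | 0.047 |
| 6 | 1 | 0.563 | 0.592 | 0.682 | 0.041 |

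The last column and the events-over-visits column use Fisher's test. The other two are exact conditional tests on event counts. Three event-level versions are shown because the plan gives no denominator.

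**Hand check of the person-time column.** Relative to independent events, the variance of the total is inflated by 1 + d·m·E[T²]/E[T], where E[T²]/E[T] = 2.83/1.49 = 1.90 years. The rejection rate is then about 2[1 − Φ(1.96/√inflation)].

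- m = 0.5, d = 1: inflation 1.95, rejection 0.16 (simulated 0.160).
- m = 3, d = 0.5: inflation 3.84, rejection 0.32 (simulated 0.325).
- m = 6, d = 1: inflation 12.4, rejection 0.58 (simulated 0.563).

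**Design survival effect present, event rates per unit time identical.** Fisher's test on subjects with at least one event rejects in 0.075 to 0.145 of trials over the same range of m and d.

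**Alternative for totals.** A rate ratio with person-time as offset and subject-level robust variance (4000 replicates, m = 0.5 to 6, d = 0.5 to 1) rejects in 0.047 to 0.058 of trials with equal survival, and in 0.055 to 0.057 under the design survival effect.

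**The case against.** The strongest reply is that this is loose wording. Fisher's test requires a two-by-two table, the preceding sentence speaks of occurrence, and an experienced analyst would count subjects with and without an event. On that reading the test held its size with equal survival (0.040 to 0.048). The high rejection rates belong only to the event-level reading and to assumed event rates. Individual adverse event terms and laboratory abnormalities may well be rare, and at 0.15 per year the event-level rejection rate is 0.04 to 0.09.

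Much of this stands. A reader might infer that the safety p-values are bound to be invalid. The documents do not support that, because they never say that events are the units. A reader might also infer that follow-up of 12 to 36 months invalidates the test by itself. It does not: randomization balances planned follow-up, and the subject-level results above were obtained with it varying. Only follow-up that differs by arm distorts a subject-level comparison.

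Nor is the direction of that distortion certain. Longer survival on drug lengthens observation. After drug is stopped, section 6.2.3 names ALSFRS-R and vital status every 8 weeks and encourages a full visit every 16 weeks, against four-weekly visits otherwise, so heavier withdrawal on drug could hide events.

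The reply does not remove the point. Two analysts could produce different results from the same sentence, and the benign reading is still distorted if the drug works as designed. With progression symptoms recorded as adverse events, an overall comparison of subjects with any event would probably be close to 100% in both arms and say little. Section 9.1.3 also plans treatment-by-gender and treatment-by-ethnicity interaction tests in the safety analyses, which Fisher's test does not provide.

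**Conclusion.** The point holds as a defect of definition, with consequences that depend on how the sentence is carried out. With events as units and between-subject variation, false positives run at about 0.16 to 0.68 for assumed rates of 0.5 to 6 per subject-year, and there is little or no inflation at low rates without such variation. With subjects as units, size is kept under equal survival. Under the design hazard ratio of 1.5, a difference is flagged in about 0.075 to 0.145 of trials although event rates are identical, because follow-up is about 10% longer on drug.

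These figures rest on assumed event rates and heterogeneity and on the simplified follow-up described above. The consequence is limited. The efficacy and futility rules use survival, ALSFRS-R, accrual and treatment discontinuation, safety stopping rules are left to the DSMB, and no alpha or primary conclusion is tied to this comparison. The change is still worth making, because long-term safety is a stated outcome and the remedy is cheap.

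**What to change.** Amend the safety paragraph of section 9.1.3 as follows.

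- (a) State that Fisher's exact test compares the number of subjects with at least one event, for each adverse event term and each laboratory abnormality, in a common window such as the first 52 weeks. The window narrows the exposure gap under the design effect but does not remove it. Mean first-year follow-up would be 0.25/0.288 = 0.87 years on placebo and 0.175/0.192 = 0.91 years on drug, about 5% longer rather than 10%.
- (b) Compare totals with a negative binomial model or a robust-variance rate model, with log follow-up time as offset. The planned interaction tests can be added to the same model.
- (c) If time to first event is analysed, use cause-specific hazards with censoring at death. Cumulative incidence alone would keep the survival artefact. With an event hazard of 0.5 per year in both arms, three-year incidence is 0.5/(0.5 + h) × [1 − exp(−3(0.5 + h))], which is 57% at h = 0.288 and 63% at h = 0.192.
- (d) Tabulate events that are symptoms of ALS progression separately.

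This needs no new assessments beyond what the sites already record. The cost is some extra programming and a longer set of safety tables.

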## 2.2.2 Safety and Clinical Use of Ceftriaxone in Humans

Ceftriaxone is generally well tolerated and severe adverse events have only rarely been reported. Over 100 million people have received ceftriaxone for the treatment of a variety of infections. Few patients have received ceftriaxone for more than six weeks. Ceftriaxone is not approved by the Food and Drug Administration (FDA) for treatment longer than 4-6 weeks. Toxicities of ceftriaxone are similar to those reported with other cephalosporins and include pseudomembranous colitis, super-infections, local pain on administration, phlebitis, fever,

pruritis, rashes, anorexia, nausea, vomiting, diarrhea, and abdominal pain. There is no evidence of teratogenicity in rodent study or in primates. There are no adequate studies in pregnant women.

Across many studies, the most frequently observed adverse events during treatment with ceftriaxone are hematological, including eosinophilia (6%), thrombocytosis (5.1%), leukopenia (2.1%), and thrombocytopenia (1%); however these adverse reactions have been reversed when drug administration was stopped [103]. Gastrointestinal adverse events during ceftriaxone therapy, primarily diarrhea (2.7%), are common. Ceftriaxone is also excreted via the bile leading to high biliary concentrations of the drug. Biliary adverse effects include the formation of biliary sludge leading to biliary obstruction, cholecystitis, choledocholithiasis, and pseudolithiasis. Prolonged use of ceftriaxone may result in overgrowth of nonsusceptible organisms. Neutropenia has been reported with ceftriaxone use. In one series, the mean time to develop neutropenia was 21 days (range 8-25 days). It was reversible upon discontinuation of the medication. The frequency of hypersensitivity skin reactions to ceftriaxone is between 1 and 3%; anaphylaxis is rare. The risk of anaphylaxis may be increased with a history of allergy to penicillin and is certainly increased with a history of allergic reaction to cephalosporin. Ceftriaxone is contraindicated in patients with known hypersensitivity to penicillins or cephalosporins. Nonconvulsive status epilepticus has been rarely reported with ceftriaxone use and is more common in patients with renal failure [104].

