All cephalosporins are potentially nephrotoxic, especially at high doses [105]. It is recommended that renal function and electrolytes should be monitored following very large doses of cephalosporins, or if administered for an extended period of time. The most common nephrotoxic effects of cephalosporins are acute allergic interstitial nephritis (AIN) and acute tubular necrosis (ATN) [106]. Clinically, acute allergic interstitial nephritis can present with rash, fever, arthralgias, eosinophilia, or just isolated acute renal dysfunction with a rising BUN and creatinine. Proteinuria is generally less than 2 grams/day. Urinalysis may be remarkable for white blood cells and white blood cell casts, (with a negative urine culture) and the presence of eosinophils by Wright stain. Renal biopsy typically shows a marked interstitial inflammatory infiltrate with lymphocytes, plasma cells, and eosinophils, as well as edema with focal tubular damage. On occasion, epithelioid granulomas with giant cells may be seen within the interstitium. Generally, symptoms occur 2 weeks after initiation of therapy, although this has been reported to vary from 2 to 60 days [107]. Discontinuing the offending agent plus the addition of steroids may be indicated if renal dysfunction is severe or oliguria occurs. The second pattern of injury that can be seen with cephalosporins is acute tubular necrosis (ATN). This can be manifested by the presence of pigmented granular casts on microscopic examination of the urinary sediment, as well as a rising blood urea nitrogen and serum creatinine. This process is generally reversible if the drug is discontinued [106].

There are only a few published studies of ceftriaxone administered at 4 grams per day [108, 109]. Treatment duration was between 10 and 14 days. No serious adverse events were reported. Twenty-three patients with clinically active late Lyme disease were randomized to intravenous treatment with either penicillin or ceftriaxone (2 grams bid; N=13) for 14 days. After 23 patients were treated, they prospectively treated an additional 31 patients with ceftriaxone; 17 with 4 grams per day, and 14 with 2 grams per day for 14 days. Ceftriaxone was generally well

tolerated. None of the patients experience serious side effects, but mild to moderate diarrhea developed in about half of those receiving 4 grams per day and in about 10% of those treated with 2 grams per day [110].

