## **Biliary Sludge**

Biliary sludge may occur with long-term ceftriaxone use, but is rare with short-term use and occurs in less than 0.1% of patients treated [103]. It may occur more frequently with long-term use. Often, patients are asymptomatic. Symptoms of biliary tract disease, such as acute cholecystitis, are rare. When symptoms of biliary tract disease do manifest, they can present as right upper quadrant abdominal pain, tenderness, fever, jaundice and elevated bilirubin and alkaline phosphatase [172]. Biliary sludge can be diagnosed by abdominal ultrasound. Subjects with cholelithiasis diagnosed by abdominal ultrasound can be referred to a site gastroenterologist. All subjects will undergo abdominal ultrasounds at Week 4, Week 8, and Week 20. A detailed management plan is provided to the sites in the manual of operations.

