## **8. CRITERIA FOR INTERVENTION SUSPENSION, RECHALLENGE, OR PERMANENT DISCONTINUATION**

### **8.1 Intervention Suspension Related to Ceftriaxone Use**

**Study drug will be suspended under the following circumstances:**

(Please refer to the Manual of Operations for details regarding management of AEs)

- If the subject has *C. difficile* infection and is concurrently systemically ill with fever, leukocytosis or if the symptoms are refractory to treatment
- If the *C. difficile* infection results in pseudomembranous colitis
- If the subject is being treated for severe dehydration
- If the subject is symptomatic from biliary sludge
- If the subject is diagnosed with symptomatic cholelithiasis
- If the subject is diagnosed with invasive candidiasis
- If the subject is diagnosed with acute interstitial nephritis
- If the subject is diagnosed with acute tubular necrosis
- If the subject is diagnosed with renal failure
- If the serum creatinine doubles as compared to the screening visit value, the test will be repeated. If the value is confirmed (doubled as compared to screening visit value), study drug will be suspended while subject is evaluated.
- If the urinalysis is positive for Wright's or Hansel's stain as this is suggestive of eosinophiluria, or allergic interstitial nephritis
- If the spot urine protein is greater than 1000 mg. This is likely an indication of severe renal toxicity
- If the subject becomes oliguric, which is defined as urine output less than 500 mL/day. This can be an indication of severe renal toxicity
- If the Absolute Neutrophil Count (ANC) is less than 1.2 th/cmm

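### Measured laboratory values are summarised only as change to the final visit, which is badly placed for early reversible abnormalities, and the accompanying Fisher comparison has no threshold and no subject-level unit

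*Combined protocol and SAP*

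**What the plan says.** The laboratory analysis is in section 9.1.3, Analysis of Secondary Outcome Variables, under Safety and Tolerability. It has three parts:

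- A test: "Total number of adverse events and abnormal laboratory tests will be compared between groups using Fisher's exact test".
- A general statement: "Withdrawal, abnormal laboratory tests, vital signs and use of concomitant medications will be assessed to characterize the safety profile of ceftriaxone".
- A summary of measured values, which the sentence presents as an addition to the other two: "Descriptive statistics denoting the changes from baseline to the final assessment visit with respect to key laboratory parameters and vital signs".

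The same paragraph compares the arms on the occurrence of each adverse event. It gives no by-visit, worst-value or shift summary, no numerical definition of an abnormal test, and no mention of ultrasound.

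Elsewhere, section 2.2.2 reports that in one series "the mean time to develop neutropenia was 21 days (range 8-25 days"), reversible on stopping. Of interstitial nephritis it says: "Generally, symptoms occur 2 weeks after initiation of therapy, although this has been reported to vary from 2 to 60 days". Section 8.1 lists laboratory grounds for suspension, including an absolute neutrophil count (ANC) below 1.2 th/cmm and a confirmed doubling of creatinine: "If the serum creatinine doubles as compared to the screening visit value, the test will be repeated". Section 6.2.2 has safety laboratory tests at screening, weeks 1, 2 and 4, and every four weeks after that. On imaging, section 7.1 (Biliary Sludge) says: "All subjects will undergo abdominal ultrasounds at Week 4, Week 8, and Week 20".

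**The concern.** A change from baseline to the last visit describes where a laboratory value ended up. It says little about an abnormality that appeared in the first two months, led to suspension of drug, and resolved. Section 2.2.2 describes neutropenia and the other haematological changes in this way. It gives interstitial nephritis an early onset and calls tubular necrosis generally reversible.

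The last value is also selective. It comes from subjects who are alive and attending, and the section does not say which visit counts as final for those who die or stop coming. Baseline is not defined either: the schedule of assessments shows safety laboratory tests at screening and week 1, but none at Day 0.

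What is at stake is the long-term safety description of a drug that, by section 2.2.2, few patients have received for more than six weeks. A reader of the planned tables could see almost no mean change in creatinine or ANC. How many subjects crossed a suspension limit would then rest on a Fisher comparison whose threshold and unit are not stated, and on what sites judged clinically significant.

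**Working it through.** The plan attaches no figure to the laboratory summary, so there is nothing to reproduce. The checks below ask how well the summary is placed, whether the Fisher comparison is well defined, and what the change would gain.

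**Share of the data used** (visit schedule, section 6.2.2). Post-baseline draws are weeks 1 and 2 plus every fourth week:
- by week 52: 2 + 52/4 = 15
- by week 104: 2 + 104/4 = 28
- by week 156: 2 + 156/4 = 41

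The final visit is one of these. Four draws (weeks 1, 2, 4 and 8, that is days 7, 14, 28 and 56) fall inside the 60-day window for interstitial nephritis.

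**Timing** (onset from section 2.2.2; follow-up of 12-36 months from section 6.3.4).
- Day 25, the upper limit for neutropenia: 25/365 = 7% of a 12-month follow-up and 25/1095 = 2% of a 36-month one.
- Day 60: 60/365 = 16% and 60/1095 = 5%.

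**Selection** (section 9.1.3, Stopping for Efficacy). By month 39 the plan expects 243 to 293 subjects of 600 to have died, had a tracheostomy or started permanent assisted ventilation (PAV): 243/600 = 41% and 293/600 = 49%. Section 6.3.4 says fewer than 10% of patients elect PAV, so most of these should be deaths. Subjects who have died have no end-of-study laboratory value.

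**Dilution of a mean** (illustration; rates assumed). If a share s of an arm doubles its creatinine and a fraction u remains unrecovered at the last visit, the arm mean rises by s × 100% × u of baseline. With s = 2% and u = 10%, that is 0.2%. Even at the peak (u = 1) it is only 2%. So worst values should be shown as a distribution with counts of limit crossings, not only as a mean.

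**Unit of the Fisher comparison** (illustration; counts assumed). Suppose 8 of 400 ceftriaxone and 1 of 200 placebo subjects are ever abnormal, each at 3 of 15 draws.
- By subject, 8/400 against 1/200: p = 0.28.
- By test, 24/6000 against 3/3000: p = 0.013.

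The same subjects give opposite answers. The second is not valid, because repeated draws on one subject are not independent.

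**Power of a subject-level comparison** (exact Fisher, two-sided 0.05, 400 against 200; placebo rates assumed). Section 2.2.2 gives leukopenia 2.1%, thrombocytopenia 1% and eosinophilia 6%. Section 7.1 gives interstitial nephritis and tubular necrosis each below 1%.

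| Ceftriaxone | Placebo | Power |
|---|---|---|
| 1% | 0% | 2% |
| 2% | 0% | 41% |
| 2% | 0.5% | 17% |
| 2.1% | 0% | 46% |
| 2.1% | 1% | 9% |
| 5% | 0.5% | 92% |
| 5% | 1% | 75% |
| 6% | 0% | about 100% |
| 6% | 1% | 89% |

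The 5% rows are a what-if, well above the renal rates that the protocol cites. If only 10% of the excess abnormalities persisted to the last visit, power from final-visit status alone would be 0-3% in the four 2.1% and 6% rows.

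**The case against.** The strongest reply is that the final-visit summary is explicitly an extra. The same paragraph compares abnormal laboratory tests between arms, with no restriction to the final visit, and compares the occurrence of each adverse event. Section 10.4 counts a clinically significant abnormal laboratory finding as an adverse event. Section 10.4.1 includes abnormalities that require intervention, which a suspension under section 8.1 plausibly would. Adverse events are graded by CTCAE, and section 9.4.1 gives the DSMB laboratory frequencies during the trial. All of this stands.

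A reader might therefore infer too much: that laboratory safety rests on the final-visit change alone, or that the known harms would go unseen. The documents do not support either reading. Nor are all the harms early and transient. The renal monitoring in section 2.2.2 was prompted by a 26-week baboon study with interstitial fibrosis, and tubular necrosis is only generally reversible, with no onset time given. Section 6.2.4 stops drug at the final visit, so values there are on-drug for subjects still treated and could show persistent renal injury. Section 2.2.2 gives no onset or reversal data for bilirubin or ALT.

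It is also tempting to say that the ultrasounds were introduced because biliary events reached 26% in Stages 1 and 2. No section says so. Section 5.1.2 gives ursodiol as the response to that rate, and section 6.2.2 says only that the scans monitor for biliary disease. Sludge and stones are named adverse experiences and can enter the adverse-event comparison.

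The reply does not supply a threshold or a valid unit for the Fisher comparison, or a summary of measured values at any other time. The adverse-event route depends on site judgement where no intervention follows.

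**Conclusion.** The point holds as a weakness in how laboratory safety will be described. The single summary of measured values uses one draw in about 15 to 41, lies well beyond the stated onset windows, and is missing at study end for those who have died. The Fisher comparison could cover the gap but is under-specified: the unit alone moves p from 0.28 to 0.013 in the illustration. Asymptomatic ultrasound findings have no planned analysis of their own.

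The size is modest. No primary conclusion, clinical rule or data collection is affected. Better tables would not make rare events detectable: at 1-2% the power is 2% to 46%, depending on the assumed placebo rate. The draw counts, timing and expected events come from the protocol; the dilution, unit and power figures rest on the stated assumptions.

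**What to change.** In section 9.1.3, Safety and Tolerability:

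1. For creatinine, ANC, bilirubin and ALT, make the worst post-baseline value per subject, by arm, the main summary, shown as a distribution. State that baseline is the screening draw, which section 8.1 already uses as the reference for creatinine.
2. Run Fisher's exact test on subjects with at least one crossing of a pre-stated limit. For creatinine and ANC, use the limits already in section 8.1. For bilirubin and ALT, section 8.1 has none. The section 4.2 screening values (1.5 and 3.0 times the upper limit of normal) can serve as analysis cut-offs, labelled as taken from the eligibility criteria and not as suspension rules.
3. Tabulate new sludge or stones by arm at weeks 4, 8 and 20, relative to the screening ultrasound.
4. Keep the change to the final visit as a supplement, and define the final assessment visit for subjects who die or stop attending.

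The cost is revised analysis wording and a few tables from data already collected. No visit, test or clinical rule changes.
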